### Recruitment {15}

Participants will be selected from the caseloads of six organizations affiliated with the Academic Collaborative Center Living with an intellectual disability (AWVB) at Tranzo, Tilburg University. Eligible individuals with MID who are not currently receiving substance abuse treatment will be identified through a random selection process carried out by the principal researcher. From this pool, 138 people with MID meeting the inclusion and exclusion criteria will be pre-assigned to either the experimental or control group using a Zelen design. The randomization process will be conducted by the principal researcher in an independent capacity to ensure objectivity and minimize bias. The intervention will be delivered by behavioral specialists from the six participating healthcare organizations to ensure standardized implementation across all sites.

## Assignment of interventions: allocation

### Sequence generation {16a}

The study uses a Zelen pre-randomization design. Participants are individually randomized 1:1 to Beat the Kick or care-as-usual (CAU) using a centralized, computer-generated sequence with permuted blocks of variable size, stratified by addiction type (alcohol vs. cannabis/other drugs) to maintain balance across strata. Randomization is not clustered; clients from the same team may be allocated to either arm.

To minimize provider contamination while preserving individual randomization, trainers are assigned exclusively to a single arm (intervention or CAU) and do not deliver care in the other arm during the trial. Trainer and site identifiers are recorded at allocation; trainer will be modeled as a random effect in mixed-effects analyses to account for provider-level clustering. Any unavoidable cross-coverage will be documented a priori and examined in sensitivity analyses.

### Implementation {16c}

The primary researcher (in the role of data manager) at Tranzo will generate the allocation sequence using a computer-based random number generator. The primary researcher will also handle participant enrollment and obtain informed consent.

Once baseline assessments are completed, participants will be assigned to either the Beat the Kick or CAU group according to the allocation sequence. The principal researcher will oversee this process to ensure strict adherence to the randomization protocol and accurate group assignments.

## Assignment of interventions: blinding

### Who will be blinded {17a}

Due to the use of a Zelen design, participants cannot be blinded to their group assignment, as they are informed of their allocation after randomization. To mitigate potential analysis bias, the principal researcher, who will conduct the statistical analyses, will remain blinded to group assignments. Randomization will be implemented via a centralized computer-generated sequence; the resulting allocation key will be generated and securely stored by a trial coordinator who is not involved in the statistical analyses. For the purpose of analysis, the dataset will include only coded group labels (e.g., “Group A” and “Group B”), without fields that could reveal allocation. The key linking these codes to the actual arms will remain inaccessible to the analyst until all primary analyses are complete. This approach preserves the integrity of the randomization process and ensures unbiased statistical conclusions. The Zelen design further reduces selection bias and enhances external validity by simulating real-world clinical scenarios [37].

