**Methods:**

Open-label, multicenter superiority randomized controlled trial in the Netherlands. We will recruit 138 adults (≥ 18 years) with MID or borderline intellectual functioning (intelligence quotient (IQ) 50–85 with adaptive limitations) and hazardous substance use (Alcohol Use Disorders Identification Test (AUDIT) ≤ 19 or Drug Use Disorders Identification Test (DUDIT) ≤ 24; ≥ 12 months) from six intellectual-disability care organizations. Recruitment will be conducted jointly by researchers from Tilburg University and care professionals at the participating organizations. In a Zelen pre-randomization design, eligible clients will be randomized 1:1 to Beat the Kick or CAU using a centralized computer-generated sequence with variable block sizes, stratified by addiction type (alcohol vs cannabis/other drugs). Tilburg researchers will obtain informed consent after allocation (intervention: consent for intervention + assessments; CAU: consent for assessments only). As an open-label trial, only the statistical analyst will remain blinded to allocation via A/B-coded datasets; the allocation key is held by an independent coordinator until primary analyses are complete. Assessments occur at T1 (pre), T2 (post), T3 (1 month), and T4 (6 months). Safety is monitored at T2–T4 through systematic adverse event (AE) and serious adverse event (SAE) recording, and serious events are reported to the Ethics Review Board within 24 h.Primary outcome: autonomous motivation (Treatment Self-Regulation Questionnaire; 15 items; 1–5 scale). Secondary outcomes: substance use ( Substance Use and Misuse in Intellectual Disability Questionnaire (SumID-Q) with AUDIT (0–40; ≥ 8 hazardous; ≥ 20 probable dependence) and DUDIT (0–44; ≥ 6 men/ ≥ 2 women hazardous; ≥ 25 probable dependence)), satisfaction and frustration of psychological needs (Basic Psychological Need Satisfaction and Frustration Scale – Intellectual Disability Version (BPNSFS-ID); 24 items; 1–5), treatment engagement (yes/no), and participant satisfaction. Primary analyses will use intention-to-treat linear mixed-effects models with fixed effects for group, time, and group × time, adjusting for the stratification variable.

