### Trial design {8}

This multicenter, parallel-group superiority randomized controlled trial employs a Zelen design to evaluate the effectiveness of the Beat the Kick intervention in enhancing autonomous motivation and reducing substance use among adults with MID. The Zelen design ensures unbiased group assignment by randomizing 138 consecutive participants into two groups—treatment and CAU—prior to obtaining informed consent, thereby minimizing selection bias and mirroring real-world clinical scenarios [23]. Participants are allocated in a 1:1 ratio, with 69 individuals in each group.

Randomization occurs at the individual level, which introduces the potential risk of carry-over effects if therapists treat participants in both the CAU and Beat the Kick intervention groups. To mitigate this risk, therapists are exclusively assigned to either the intervention or CAU group, ensuring no overlap in their caseloads. Additionally, therapists from the intervention and CAU groups are employed by different organizations and do not collaborate or exchange information during the study period. This separation prevents contamination and enhances the validity of the findings. Following the study, therapists can provide valuable reflections on their experiences with the training, including its perceived effectiveness and practical applicability, offering further contextualization of the outcomes.

Assessments are conducted at four time points: pre-treatment (T1), post-treatment (T2), and follow-up evaluations at 1 month (T3) and 6 months (T4) after the intervention. This schedule allows for the measurement of both immediate and sustained effects of the intervention.

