Potential confounders, such as living arrangements (e.g., 24-h supervised care, outpatient services, or home-based support) and prior substance use treatment exposure, will be incorporated as covariates. These factors are expected to influence engagement and outcomes by shaping daily routines, support systems, and environmental stability. Trainer effects, which may vary due to differences in style, experience, or engagement, will be modeled as a random effect to minimize potential bias. Additionally, to prevent carry-over effects, trainers will be exclusively assigned to the intervention group, ensuring that training specific to Beat the Kick does not unintentionally influence CAU.

The secondary objective is to evaluate the intervention’s effectiveness in reducing substance use among adults with MID. It is hypothesized that the experimental group will show a greater reduction in substance use levels compared to the CAU group at follow-up. LMMs for secondary outcomes will mirror the primary model, including addiction type as a fixed effect (with exploratory interactions), and will adjust for baseline substance use levels.

To accommodate the Zelen design’s pre-randomization process, analyses will carefully consider group allocation at the pre-randomization stage, ensuring that group comparisons accurately reflect the intervention’s true effect. Sensitivity analyses will assess the robustness of results, including tests with and without outliers. Missing data will be handled using full information maximum likelihood (FIML), a robust method that leverages all available data and is generally preferred regardless of the underlying missingness mechanism [47]. Although FIML does not eliminate all bias under not-missing-at-random (NMAR) conditions, it typically yields less biased results than listwise deletion. Conclusions drawn under NMAR will be interpreted with appropriate caution, and the plausibility of the missing at random (MAR) assumption will be evaluated in light of the observed data structure and auxiliary variables.

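### The analyst's A/B masking conflicts with the trainer random effect unless trainer codes are neutral in both arms, and the protocol disagrees on whether CAU has trainers

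*Protocol article*

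**What the plan says.** **Masking.** The abstract (Methods) says that "only the statistical analyst will remain blinded to allocation via A/B-coded datasets". Who will be blinded {17a} adds that the file carries coded group labels, "without fields that could reveal allocation. The key linking these codes to the actual arms will remain inaccessible to the analyst" until the primary analyses are finished. Procedure for unblinding {17b} repeats that only the data analysts are blinded.

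**Model.** Sequence generation {16a} records trainer and site identifiers at allocation and states that "trainer will be modeled as a random effect in mixed-effects analyses to account for provider-level clustering". Statistical methods {20a} says the same of trainer effects, which "will be modeled as a random effect to minimize potential bias". It also has the secondary models mirror the primary one.

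**Where trainers exist.** The sections differ:
- {20a}: "trainers will be exclusively assigned to the intervention group, ensuring that training specific to Beat the Kick does not unintentionally influence CAU".
- {16a}: "trainers are assigned exclusively to a single arm (intervention or CAU) and do not deliver care in the other arm during the trial".
- Trial design {8}, speaking of therapists: "therapists are exclusively assigned to either the intervention or CAU group, ensuring no overlap in their caseloads".

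**The concern.** A variable that the primary model needs must be in the analyst's file before the key is released. If that variable is tied to arm, it can carry the information that the A/B coding is meant to hide. Trainer is tied to arm under every version in the protocol, because no trainer works in both arms.

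The stake is the truth of the trial's one blinding statement. The primary outcome is an interviewer-assisted self-report in an open-label trial. Some analysis decisions are also left open: covariates are introduced by example, influential points are examined where needed, and the plausibility of missing at random is judged from the data. If the labels can be read from the file, a published statement that the analysis was blinded would be wrong. If the file really excludes every revealing field, the stated model may not be runnable on it.

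**Working it through.** The plan gives no figure on this point, so the check compares sections, with a simple count.

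**Inputs**
- Arm sizes: 138 participants at 1:1, so 138/2 = 69 per arm ({8}).
- Key withheld until all primary analyses are complete ({17a}).
- Trainer is a random effect in the mixed models ({16a}, {20a}).
- Location of trainers: intervention only ({20a}), or one arm each, which may be CAU ({16a}; {8} for therapists).

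**Step 1: timing.** The primary analysis uses trainer, and the key comes out only after that analysis. The trainer field must therefore be in the file while the analyst is supposed to be masked. This holds under any reading.

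**Step 2: if {20a} governs.**
- Label for Beat the Kick: trainer filled for 69/69 = 100%.
- Label for CAU: trainer filled for 0/69 = 0%.

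Both labels are decoded at sight, for 69 + 69 = 138 participants. Complete data are not needed: if CAU has no trainers, a single filled entry under one label identifies both. Recoding trainer names does not help, because the pattern of filled and blank entries is what reveals the arm. Other sections fit this reading. Table 1 lists the trainer only for Beat the Kick sessions, Intervention description {11a} and adherence strategies {11c} tie the role to Beat the Kick training, and the CAU description {6b} names no trainer.

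**Step 3: if {16a} governs.**
- Under each label: trainer filled for 69/69 = 100%.

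Presence alone decodes nothing. Trainer is still nested in arm, however, so recognising one real trainer identifies the label for that whole arm and, by elimination, the other. Section {8} also says the two groups of therapists have different employers, so site may point the same way. (Recruitment {15} has specialists from all six organizations deliver the intervention, so how strongly site would do so is unclear.) Masking and model can coexist if every participant in both arms carries a neutral provider code. Section {6b} describes CAU as possibly given by a multidisciplinary team, so it is not obvious which single code a CAU participant would carry. Blank codes would bring back Step 2.

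**Step 4: who the analyst is.** {17a} names the principal researcher as the blinded analyst and gives the key to a trial coordinator. Concealment mechanism {16b} makes the sequence accessible only to the principal researcher, who also assigns participants. Implementation {16c} has the primary researcher generate it. An analyst who knows the allocations is not masked by any treatment of the trainer field. Conversely, appointing a different analyst leaves Steps 2 and 3 unchanged. The two problems are separate and both need repair.

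**The case against.** A reader might infer that trainer certainly exists only in the Beat the Kick arm, so that the masking and the model can never both hold and every row is always decoded. The documents do not support that. {16a}, the section that specifies the random effect together with the recording of identifiers, allows trainers in CAU, and {8} has therapists in both arms. The {20a} clause is about carry-over and could mean only that Beat the Kick trainers do not serve CAU. On that reading neutral codes would be enough, and the presence of a code decodes no rows.

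It can also be said that no section sends trainer names to the analyst, that site is not in the model and can be withheld, and that recoding is a detail for an analysis plan or data management plan. This stands in part: the absence of a recoding rule is not in itself a fault. What remains is that the protocol makes two positive statements that collide, and disagrees with itself on the fact that decides whether recoding can work.

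A further tempting inference is that lost masking would bias the primary result. The documents do not show this. Influential points are handled by sensitivity analyses with and without them, and the main covariates are named in advance. The Discussion already acknowledges performance and social-desirability bias, which analyst masking would not remove.

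**Conclusion.** The concern holds conditionally. As written, the protocol promises a masked file free of revealing fields and requires an arm-nested variable in the analysis of that file, without reconciling the two. If trainers exist only in the intervention arm, all 138 participants are decoded whenever the trainer field is supplied. If providers are coded in both arms, none are decoded by presence, and masking depends on neutral codes and on withholding real trainer and site identities. The primary model and the secondary models that mirror it are affected alike.

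This rests on the trainer effect being fitted as stated and on the key being held until the primary analyses end. It concerns the truth of the blinding claim, not a demonstrated bias in the treatment effect. Repairing the trainer field alone would not make the claim true while {16b} and {16c} give the sequence to the role that {17a} names as blinded analyst.

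**What to change.** 1. Reconcile {16a}, {8} and {20a} on whether CAU participants have a trainer or provider identifier.
2. If they do, have the coordinator assign neutral provider codes in both arms, and keep site and real identifiers out of the analysis file until the primary analyses are complete.
3. If they do not, drop the A/B masking claim for models with trainer. Write the primary script in full (model, covariates, influential-point rule), test it on a file with shuffled arm and dummy trainer codes prepared by the coordinator, and date and archive it. Then release the true fields and run it unchanged. Correct the abstract, {17a} and {17b} to say that analysis choices were fixed before unmasking.
4. Under either route, reconcile {16b} and {16c} with {17a} so that the analyst does not hold or generate the sequence.

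The cost is wording, one prepared file and, under step 3, a slightly less favourable blinding statement. Nothing in the design, sample size or treatment comparison changes.

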### Procedure for unblinding if needed {17b}

As this study is open-label and only the data analysts are blinded, no unblinding procedures will be required.

## Measures

### Plans for assessment and collection of outcomes {18a}

The primary outcome of this study, autonomous motivation, will be assessed using an adapted version of the TSRQ specifically tailored for substance abuse [21]. The TSRQ comprises 15 items divided into four subscales: autonomous motivation (e.g., “I would change my use because I choose to”), controlled motivation (e.g., “I would change my use because others expect me to”), and amotivation (e.g., “I am not at all concerned about why I would change my use”). Participants will respond on a 5-point scale from “completely untrue” to “completely true.” Mean scores for each subscale will be calculated by summing the corresponding items and dividing by the number of items. Previous studies have demonstrated strong reliability for the TSRQ, with Cronbach’s alpha values exceeding 0.73 for most subscales; however, amotivation has a lower reliability (α = 0.41). Autonomous motivation is associated with positive health outcomes, whereas controlled motivation correlates with negative outcomes [26].

Psychological need satisfaction and frustration will be measured using the BPNSFS-ID [35], adapted from the original BPNSFS [38]. This scale evaluates satisfaction and frustration across three psychological needs: autonomy, relatedness, and competence, comprising 24 items (eight items per need). Responses are rated on a 5-point Likert scale from 1 (“completely untrue”) to 5 (“completely true”). The BPNSFS-ID demonstrates high internal consistency (overall Cronbach’s alpha = 0.92) and robust factorial structure, with subscale alphas ranging from 0.78 to 0.92 and test-retest reliability ranging from 0.68 to 0.83 over two weeks. This study aims to explore whether the intervention influences substance use by impacting the satisfaction or frustration of these needs, potentially elucidating mechanisms underlying the intervention’s effectiveness.

Substance use will be assessed using the Substance Use and Misuse in Intellectual Disability Questionnaire (SumID-Q) [23]. This structured instrument follows a stepwise approach: it first identifies substances familiar to the participant (e.g., tobacco, alcohol, cannabis), then explores knowledge, attitudes, and contextual influences, and finally addresses personal use in a non-threatening manner, supported by visual aids to enhance understanding. The SumID-Q is specifically designed for individuals with MID and BIF, using simplified language, clear sentence structures, and visual support. Psychometric studies [23, 39] demonstrate adequate internal consistency and test–retest reliability. The embedded AUDIT and DUDIT scales have also shown good reliability: Cronbach’s α = 0.70 and 0.86 [40]. These findings support the SumID-Q as a valid and accessible tool for assessing substance use in individuals with MID-BIF, minimizing bias and facilitating accurate reporting (Table 2).

**Table 2 Tab2:** Measures

	***Measures***				***Measurement***			
	Measure	Items (−/+)	Respondent	Type	T(1)	T(2)	T(3)	T(4)
Motivation and psychological needs	TSRQ	15	Participant	Questionnaire	*	*	*	*
	BPNSFS-ID	24	Participant	Questionnaire	*	*	*	*
Substance use	SumID-Q (Base form)	30	Participant	Questionnaire	*	*	*	*
	SumID-Q (Alcohol module)	49–61	Participant	Questionnaire	*	*	*	*
	SumID-Q (Tobacco module)	39–51	Participant	Questionnaire	*	*	*	*
	SumID-Q (Cannabis module)	50–62	Participant	Questionnaire	*	*	*	*
Total items, participant		108–131			108–131	108–131	108–131	108–131

Treatment engagement, defined as whether a participant has initiated a formal treatment program following the intervention, will be recorded as a binary outcome (yes/no). This will be assessed at post-intervention follow-up, using a combination of self-report and verification through the referring care provider or treatment records. This outcome will serve as a behavioral indicator of the participant’s motivation to engage with care and will support the interpretation of the intervention’s practical impact. Pre-treatment assessments will also document the number of prior treatments participants have undergone. This variable will be analyzed to determine its impact on participants’ readiness and responsiveness to the intervention. Understanding participants’ treatment history will provide insights into how prior experiences influence the effectiveness of Beat the Kick and may help identify subgroups that benefit more from specific strategies.

All assessors will undergo rigorous training to ensure consistent administration of these questionnaires, led by the primary researcher. Data collection forms and instruments will be securely stored on a protected online platform accessible only to the research team.

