In addition, treatment engagement will be captured as initiation of formal SUD treatment (yes/no)—defined as attending ≥ 1 treatment session or completing an intake—within the T3 window (± 1 month post-T2); follow-through on referrals (yes/no) will be recorded separately. Participant-reported acceptability will be assessed at T2 using brief Likert-type items (e.g., clarity, relevance, burden, usefulness, overall satisfaction; 1–5) and open-ended feedback. Safety will be monitored by systematic recording of intervention-related adverse events (AEs) and serious adverse events (SAEs) at T2, T3, and T4 via structured checklists and open queries; definitions, ascertainment procedures, and reporting timelines are detailed in Harms {23}.

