### Sample size {14}

A sample size power analysis was performed using G*Power 3.1.9.7 [36] to ensure the study’s feasibility within its constraints and the available population of individuals with mild intellectual disabilities (MID) who abuse substances. The calculation was based on the primary hypothesis, which posits that participants receiving the Beat the Kick intervention will show greater improvement in autonomous motivation compared to those in the control group. The analysis assumed a between-group design with four measurement points: pre-treatment (T1), post-treatment (T2), and follow-ups at 1 month (T3) and 6 months (T4). An effect size of *f* = 0.25 (medium effect), a power of 80%, and a significance level of 5% (two-sided) were used, with default settings for the correlation among repeated measures (0.5) and the non-sphericity correction (ε = 1, assuming sphericity).

The power analysis indicated that a sample of 82 participants is required to detect the expected effect with 80% power. Given the elevated risk of dropout among individuals with MID and co-occurring substance use—estimated at approximately 40% based on previous studies—the recruitment target was increased to 138 participants.

This adjusted target accounts for anticipated attrition and ensures that a sufficient number of participants will complete the study to maintain statistical power. Although recruiting 138 individuals from this population poses logistical challenges, it is considered feasible through targeted recruitment strategies, including partnerships with care providers and the use of established professional networks. This adjusted recruitment plan acknowledges the inherent risks of higher dropout rates but ensures the robustness of the study’s findings and feasibility within its framework.

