### Methods in analysis to handle protocol non-adherence and missing data {20c}

The ITT principle will guide the analysis, ensuring robustness and generalizability by including all participants in their originally assigned groups, regardless of adherence to the intervention protocol or study completion. This approach minimizes biases from deviations, dropouts, or non-compliance, enhancing real-world applicability [45].

Missing data will be addressed using maximum likelihood estimation within the LMM framework. This method leverages all available data points, preserving dataset integrity while accounting for randomness in missingness without requiring imputation [46]. Combining ITT with maximum likelihood estimation ensures a comprehensive and unbiased assessment of the intervention’s effects.

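### Treatment engagement is collected by self-report at follow-up with records named only as verification, and no rule makes records the source when the T3 contact is missed

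*Protocol article*

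**What the plan says.** Outcomes {12} makes treatment engagement a binary secondary outcome, "defined as attending ≥ 1 treatment session or completing an intake", counted in the T3 window, about one month after T2.

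Plans for assessment and collection of outcomes {18a} says how it is obtained. On timing: "This will be assessed at post-intervention follow-up". On source: "using a combination of self-report and verification through the referring care provider or treatment records". Records appear there as a check on what the participant reports.

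Other sections bear on the point:

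- Sample size {14} puts dropout at a level "estimated at approximately 40% based on previous studies", and for that reason "the recruitment target was increased to 138 participants".
- Plans to promote participant retention {18b} continues follow-up for people who stop the intervention, provided they agree to stay in the study.
- Sections {11b} and {11d} say that a voluntary start of formal treatment during the study will be recorded as a meaningful outcome. {11d} adds that concurrent treatments will be documented. Neither names a source for people who no longer attend.
- Section {20c} gives the handling of missing data: "Missing data will be addressed using maximum likelihood estimation within the LMM framework". Table 3 has no row for engagement.

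**The concern.** Whether someone attended a treatment session or completed an intake is a service event. A provider or a treatment record can show it without an interview. The protocol nevertheless ties the outcome to a follow-up contact and a self-report, in a population where it expects heavy dropout. The Discussion itself says that people who drop out may differ systematically from those who stay.

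Two things are at stake. The first is precision, because every missed T3 contact without a record check is one fewer binary outcome. The second is bias. Starting treatment and continuing to attend study visits plausibly both reflect engagement, so attenders may over-represent starters. If that relation is stronger in one arm, it creates or distorts a difference in the outcome that {18a} describes as the behavioural indicator supporting the motivation result.

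The stated likelihood method offers little protection. Engagement is a status recorded once, so there are no other measurements of it from which a repeated-measures model could borrow. The data source must also be settled before collection starts, because no later analysis plan can recover a status that nobody looked up.

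**Working it through.** **1. The plan's own figures.** Inputs from Sample size {14}: f = 0.25, r = 4 measurements, correlation ρ = 0.5, two groups, two-sided 5%, 80% power. For the between-group test in a repeated-measures ANOVA, the noncentrality is λ = f²·N·r / (1 + (r−1)ρ).

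- N = 82: λ = 0.0625 × 82 × 4 / 2.5 = 8.2, power 0.808.
- N = 80: power 0.798.

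So "a sample of 82 participants is required to detect the expected effect with 80% power" reproduces. With 40% dropout, 82 / 0.6 = 136.7, which rounds up to 137, or 138 for equal arms. This also reproduces.

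**2. Outcomes at risk.** 0.4 × 138 = 55.2, so at most about 55 engagement outcomes, leaving about 83 (41 per arm). If only half of the dropout has reached the T3 contact, 27.6 are at risk and about 110 remain (55 per arm). The protocol gives no T3 figure, so this is a range and not an estimate.

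**3. Precision.** The standard error with 41.4 instead of 69 per arm is √(69/41.4) = 1.29 times as large. The protocol gives no engagement rates, so the rates below are assumptions (two-sided 5% test of two proportions).

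| Assumed rates, CAU vs Beat the Kick | 41 per arm | 55 per arm | 69 per arm |
|---|---|---|---|
| 5% vs 20% | 0.54 | 0.67 | 0.77 |
| 10% vs 30% | 0.62 | 0.75 | 0.84 |
| 20% vs 40% | 0.51 | 0.63 | 0.73 |

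**4. Bias among attenders.** Let m be the overall proportion lost, y the true engagement rate, and k the probability of loss in starters divided by that in non-starters. The loss in non-starters is a = m / ((1−y) + k·y), and the rate seen in attenders is y(1 − k·a) / (1 − m). Assume k = 0.5, so non-starters are lost twice as often.

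With m = 0.4:

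- y = 0.30: a = 0.4/0.85 = 0.471; observed 0.30 × 0.765 / 0.6 = 0.382.
- y = 0.15: a = 0.4/0.925 = 0.432; observed 0.15 × 0.784 / 0.6 = 0.196.
- y = 0.25: a = 0.4/0.875 = 0.457; observed 0.25 × 0.771 / 0.6 = 0.321.

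True rates of 30% and 15% thus read as 38% and 20%. If k = 0.5 holds in one arm and k = 1 in the other, equal true rates of 25% read as 32% and 25%, a false gap of 7 points.

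With m = 0.2 (half the dropout by T3):

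- y = 0.30: a = 0.235; observed 0.30 × 0.882 / 0.8 = 0.331.
- y = 0.15: a = 0.216; observed 0.15 × 0.892 / 0.8 = 0.167.
- y = 0.25: a = 0.229; observed 0.25 × 0.886 / 0.8 = 0.277.

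Here 30% and 15% read as 33% and 17%, and the one-arm case gives a false gap of just under 3 points. With k = 1 there is no bias at any m.

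**The case against.** The strongest objection is that the protocol never says engagement is missing when self-report is missing. Section {18a} names treatment records, and {11b} and {11d} promise to document treatment starts without tying this to an interview. Participants are clients of six care organizations that continue their care, so a provider who knows often remains in contact. This stands as far as it goes. A reader might infer that the outcome will be lost for most dropouts, but the text does not support that. It shows only that no rule covers them.

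Other strong readings also fail:

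- *Verification works only where a referral was made.* The same phrase offers treatment records as an alternative.
- *Engagement is the only outcome that needs no interview.* Adverse events under {22} also use facilitator observation and chart review.
- *Each arm's rate is uncertain by 40 points and the difference by 80.* This needs all dropout to occur before T3 and no record to be found for anyone. The 40% has no time point, and {18b} keeps following people who stop only the intervention.
- *Records would give the outcome for everyone.* People who refuse after pre-randomization or fully withdraw consent are not covered, and the completeness of the records is not stated.
- *Consent for a record check is absent.* Section {26a} describes CAU consent as limited to assessments, but the forms themselves are supplementary files that are not shown, so this can only be checked.

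It is also fair to say that the choice of model for a binary secondary outcome may be left to an analysis plan. That does not answer the point, which concerns how the outcome is collected.

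**Conclusion.** The concern holds in a limited form. As written, records verify a self-report taken at follow-up, and nothing makes them the source when the T3 contact is missed. Up to about 55 of 138 engagement outcomes are avoidably at risk. That ceiling assumes that all of the 40% is study dropout occurring by T3 and that no record is sought for those people.

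The bias figures are illustrations. They rest on assumed engagement rates and an assumed loss ratio, and they shrink with the loss: 30% and 15% read as 38% and 20% at 40% loss, and as 33% and 17% at 20%. The false difference between equal arms further needs the relation to hold in one arm only.

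The primary endpoint and the sample size are not affected. This is an inexpensive improvement to a supportive secondary outcome, and it has to be made before the data are collected.

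**What to change.** In {18a}, state that provider or treatment records are sought in the same way, for the same window, for every consenting participant in both arms. This should apply whether or not the person attends T3, and should not be limited to a referring provider. Self-report becomes a supplement. Refer to this rule from {11b} and {11d}, so that the promised documentation of treatment starts has a named source.

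Confirm that the consent wording in both arms covers the record check for people who stop interviews without withdrawing consent to record use, and add a sentence if it does not. Report the number with unknown engagement status by arm.

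The cost is some record-retrieval time, using a source the protocol already names, and possibly one consent sentence. People who refuse or fully withdraw consent remain uncovered.
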